#### Participant timeline

Participants will be assessed at baseline (T0), post-intervention (T1), and then at three (T2) and six months (T3) follow-up, as shown in Fig 1. After intervention, only NW group will be interviewed through focus groups.

**Fig 1 pone.0281007.g001:**
[figure not shown]
Timeline of recruitment, allocation and assessments. *Measured before allocation.

### Data management and dissemination

Following what is established in Regulation (EU) 2016/679, it will be strictly respected the confidentiality of personal and health data of participants. Any data relative to participants will be stored coded with an alphanumeric ID.

All paper information will be stored in locked filing cabinet in the Faculty of Physiotherapy, The University of A Coruña. The principal researcher ([name]) and the physiotherapist in charge of intervention ([name]) of this study will be the only ones with access to this data.

Results of this study will be disseminated through scientific publications (original articles, abstracts) and communications in national and international congresses. Nonetheless, in none of the dissemination strategies, the identification of participants will be revealed.

Three of the authors ([name], [name] and CJ) will compose the data monitoring committee.

### Ethics

This study has been approved by the Clinical Research Ethics Committee (CEIC) of Galicia (Spain) in July 20^th^, 2020 (code number 2019/574) (S3–S6 Appendices).

During the study, truthful and understandable information will be provided to the participants, referred to the objectives of this trial, to the procedures (during assessments and intervention), contraindications of them, and possible complications that can arise during it development (any inconvenient is expected, despite those referred from physical activity and regular healthcare practice). Both oral and written information will be provided, and informed consent will be obtained written.

Any important protocol modification will be communicated to CEIC. All changes will be registered as modifications in the clinical trial register database (www.clinicaltrials.gov) with register number NCT05482620.

### Statistical analysis

Quantitative data will be expressed as mean and SD when normally distributed and as median and quartiles (Q1-Q3) when not normally distributed. Normality will be explored with Kolmogorov-Smirnov tests. To compare outcomes between NW group and CG, ANOVA tests for repeated measures or Kruskal-Wallis tests will be used, as appropriate in function of normality of data distribution. All this data will be analysed using SPSS (IBM Corp., Armonk, NY, USA) program, version 26.00.

To analyse qualitative data, two of the researchers, following Braun et al. [61] recommendations, will deep read all transcripts and will make notes through text, to generate initial codes independently from each other. Then, the text will be re-read, searching and reviewing themes in relation to these codes, to be able to define and name the themes. After that, report can be produced. Another member of the team will check data to ensure credibility and trustworthy of findings, and through peer debriefing technique [62], researchers can be aware of their interpretation with the possibility to clean them of preconceptions or wrong assumptions. Agreement will be measured through agreement percentages, calculated as the number of thematic units in which evaluators agree divided by total number of units. Also kappa of Cohen will be used, considering >0.81 almost a perfect agreement [63].

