## Material and methods

### Study design

This is a two-arm, parallel, randomized controlled trial (RCT) to analyse the effects of an eight-week NW program plus education and usual care compared to education and usual care alone in patients with asthma (NCT05482620). Assessments will take place at baseline, after 8-weeks and then at three and six months of follow-up. This study will be conducted in A Coruña, Spain between June 2022 and June 2024. This protocol is reported according to the Standard Protocol Items: Recommendations for Interventional Trials (SPIRIT) guidelines (S1 Checklist) [27].

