### Sample size

To estimate the sample size needed, we used the tool created by the Clinic Epidemiologic and Biostatistics service from A Coruña University Hospital Complex (CHUAC) (http://bitly.ws/sDIp). This calculation was based on the 6MWT minimum clinically important difference in patients with asthma, which is set at 26 meters [33]. Using a standard deviation (SD) of 45.49 meters, obtained from a previous pilot study [34], and considering a power of 80%, an alpha level of 0.05, and a dropout rate of 15%, a total sample size of 114 is estimated (57 in each group).

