#### Secondary outcomes

Exercise tolerance will also be assessed through the number of repetitions during the one-minute sit-to-stand test (1MSTST). This test is focused in lower limb function, especially quadriceps force [38].

The secondary outcome measurements will include physical activity level (accelerometry, International Physical Activity Questionnaire -IPAQ, and patient’s diary), asthma-related symptoms and asthma control (Control of Allergic Rhinitis and Asthma Test -CARAT and patient’s diary), dyspnea (modified Medical Research Council -mMRC, and Borg scale), lung function (spirometry), handgrip strength (hand dynamometry), HRQoL (European Quality of Life Questionnaire– 5 dimensions– 5 levels -EQ-5D-5L, mini Asthma Quality of Life Questionnaire -miniAQLQ), quality of sleep (Pittsburgh Quality of Sleep Index -PQSI), treatment adherence (Test of Adhesion to Inhalers -TAI, and patient’s diary), and healthcare resources use (patient’s diary).

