### Data collection methods

All the assessments will take place at the Faculty of Physiotherapy in The University of A Coruña. Assessments will be performed by the same trained physiotherapist (different from the one in charge of interventions), blinded to the group allocation. The evaluator has been trained to perform these assessments, in which she also has previous experience. To avoid the risk that participants reveal to which group they belong during the first evaluation, the allocation will be only made after all baseline measurements and the education component. The evaluator will be also blinded during the following assessment visits. In the case this blinding is compromised due to the possible comments of the participants, this will be reported. When a participant fails an evaluation appointment, the evaluator will contact him/her in order to propose a date to a new appointment.

After reading the information sheet and signing the informed consent, an anamnesis will be performed in order to collect the sociodemographic variables (age, sex, occupation…), past history (e.g., surgical, comorbidities, etc.) and to confirm the fulfilment of the eligibility criteria.

All questionnaires, excepting IPAQ, will be self-completed by the participants after a brief explanation of the evaluator. The evaluator will be available to clarify any doubts during the questionnaires filling and at the end will check if all questions were covered.

All outcomes will be measured at baseline, postintervention, and at three and six months follow-up, except respiratory muscle strength (measured only at baseline) and treatment adherence and healthcare resources use (not analysed at baseline). Adverse effects related to following described outcomes, or during intervention, will be registered if pertinent.

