Lung function will be assessed with a spirometry following international recommendations of ATS/ERS [50]. FEV_1_, FVC, FEV_1_/FVC, forced expiratory flow at 25 and 75% of the pulmonary volume (FEF_25-75%_) and PEF will be recorded, obtained with a spirometer (Datospir® 120C, Sibelmed, Barcelona, Spain). Moreover, PEF will be assessed every day by patients in their diary. A peak-flow meter will be provided to each patient by the study.

Handgrip strength will be measured in both hands, registering data in kilograms, and using Jamar® hand-dynamometer (Performance Health, Warrenville, IL, USA) and following Mathiowetz et al. protocol [51].

HRQoL will be assessed using a generic and asthma-specific questionnaires. EQ-5D-5L has been validated in patients with asthma [52] and in Spanish population [53]. MiniAQLQ has been validated to use in this population [54], and has already been used in Spanish context [55, 56].

Quality of sleep will be assessed using PQSI, validated in Spanish [57].

Related to treatment adherence, inhaler adherence will be evaluated using the TAI, validated in patients with asthma and in the Spanish population [58]. Also, participants should note in their diary when, what and in which dosage need take medicine in order to relieve symptoms.

Healthcare resources use will be analysed as well taking in count data from patient’s diary (emergency service or unscheduled medical visits due to asthmatic symptoms).

Respiratory muscle strength will be measured by MIP and MEP, following Spanish Society of Pneumology and Thoracic Surgery (SEPAR) recommendations [59]. A digital manometer MicroRPM® (Vyaire Medical GmbH, Hoechberg, Germany), a flanged mouthpiece and the PUMA® software (Vyaire Medical GmbH, Hoechberg, Germany) will be used. At least six acceptable measurements are required and three of them should be reproductible, with less than 5% of difference between them.

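### Diary-recorded healthcare visits are event counts over unequal intervals, but the stated tests ignore observation time: a minor, cheaply mended weakness in a secondary outcome

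*Protocol article*

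**What the plan says.** The Secondary outcomes section lists healthcare resources use last, with the patient's diary as its only source. Data collection methods defines it as "emergency service or unscheduled medical visits due to asthmatic symptoms", which makes it a count of events. The same section lists "treatment adherence and healthcare resources use (not analysed at baseline") as exceptions to measurement at every assessment, so this outcome is analysed after the programme and at the two follow-up assessments.

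Study design gives the timing: "Assessments will take place at baseline, after 8-weeks and then at three and six months of follow-up". It does not say whether the three and six months run from baseline or from the end of the programme, and no counting interval for diary events is given.

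Statistical analysis has one rule for between-group comparisons: "To compare outcomes between NW group and CG, ANOVA tests for repeated measures or Kruskal-Wallis tests will be used". Which of the two tests applies is decided by whether the data look normal. Quantities judged non-normal are to be summarised by median and quartiles. No count or rate model and no observation time is mentioned.

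For participants who drop out, Data collection methods mentions asking for diary data only in the NW group.

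**The concern.** A count of events depends on how long the person was watched. When intervals differ in length, the same underlying rate gives different expected counts at each assessment, so an apparent change over time may reflect only the calendar. Counts of infrequent events are also mostly zero within a short interval. The normality rule would then point to Kruskal-Wallis, which compares independent groups and cannot combine a participant's repeated assessments. The matching summary, median and quartiles, can read 0 (0-0) in both arms even when one arm has half the visits of the other.

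The discussion links a possible reduction in emergency or unscheduled visits to lower health and social costs. The stated analysis would not produce the quantity that bears on this, a ratio of visit rates between arms.

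**Working it through.** **The plan's own figure.** The article gives no number for this outcome. Its only sample-size figure concerns the six-minute walk: 26 m, SD 45.49 m, 80% power, alpha 0.05, 15% dropout. With two-sided alpha, n = 2 × (1.960 + 0.842)² × 45.49² / 26² = 48.05 per group, and 48.05 / 0.85 = 56.5, rounded up to 57, or 114 in total. The stated figure reproduces and is untouched by this point. It leaves about 57 × 0.85 = 48 completers per arm.

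**Intervals (inferred from Study design).** If follow-up runs from the end of the programme, the intervals are about 8, 13 and 13 weeks. If it runs from baseline, they are about 8, 5 and 13. They are unequal either way. At a constant rate, a 13-week interval has 13/8 = 1.63 times the expected count of an 8-week one.

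**Assumptions.** The article gives no event rate, so control rates of 0.25 to 2 visits per person-year were tried. Counts were gamma-Poisson with dispersion 1, the true rate ratio was 1 or 0.5, and 3,000 trials were simulated per scenario. All these values are assumptions.

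**Share of zeros.** With dispersion 1, P(0) = 1 / (1 + rate × weeks/52). In the control arm:
- 0.25 per year: 96% (8 weeks), 94% (13 weeks)
- 1 per year: 1/(1 + 8/52) = 87%, and 1/(1 + 13/52) = 80%
- 2 per year: 76% and 67%

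An upper quartile of zero needs at least about 75% zeros. At 1 per year or below, the typical summary is therefore 0 (0-0) in both arms, since an NW arm with half the rate has still more zeros. At 2 per year this no longer holds for control participants in a 13-week interval.

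**Between-arm type I error (rate ratio 1).** 0.03 to 0.06 for every test examined, under both sets of intervals.

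**ANOVA time effect with a constant rate and no treatment effect (48 completers per arm).** Falsely significant in 10% to 54% of trials with 8/13/13 weeks and 17% to 91% with 8/5/13, over 0.25 to 2 visits per year. With equal intervals it is about 5%.

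**ANOVA group-by-time interaction.** Near 5% when the rate ratio is 1 (0.045 to 0.062). Under a constant rate ratio of 0.5 it rises to at most 0.07 (8/13/13) or 0.125 (8/5/13).

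**Power, rate ratio 0.5, 8/13/13 weeks.** With 48 completers per arm at 1 visit per year: about 16%, 24% and 22% for Kruskal-Wallis at the three assessments, 41% for Kruskal-Wallis on the total, 45% for a comparison of means pooled over assessments (equivalent to the ANOVA group effect), and 48% for a rate ratio.

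A second set-up took 57 per arm with 15% dropping out at uniform times, so the rate model could also use dropouts' partial follow-up:

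| Control rate per year | Kruskal-Wallis by visit | Kruskal-Wallis on total | ANOVA group effect | Rate model |
|---|---|---|---|---|
| 0.25 | 6 / 10 / 8% | 17% | 18% | 15% |
| 0.5 | 12 / 16 / 15% | 27% | 30% | 35% |
| 1 | 18 / 24 / 24% | 39% | 45% | 52% |
| 2 | 29 / 36 / 35% | 54% | 63% | 71% |

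**Information kept relative to the rate model.** Take the ratio of (1.96 + z_power)², where z_power is the normal quantile of the power. At 1 per year the rate model has (1.96 + 0.05)² = 4.03 and the ANOVA group effect (1.96 − 0.13)² = 3.34, so about 83% is kept. The same sum gives about 70% for Kruskal-Wallis on the total and 27% to 39% for Kruskal-Wallis at a single assessment.

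**The case against.** The strongest reply is that the comparison the trial is designed to make, NW against control, is not biased. Both arms share the intervals and type I error holds. That stands, and it rules out reading the unequal intervals as a source of false treatment effects at a visit.

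Three stronger readings are tempting, and the article supports none of them.

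- **That most of the information is lost.** This is true only of Kruskal-Wallis visit by visit. The normality rule makes Kruskal-Wallis likely, but nothing says it must be run on each interval separately. ANOVA is named first and keeps about 83%. Much of the single-visit gap arises from looking at 8 or 13 weeks instead of 34, not from the missing observation time.
- **That the trial will declare a spurious change from the first to the second post-baseline assessment.** The article names no test of within-person change in raw counts. The ANOVA does print a time effect, and that is distorted, but it is not the treatment question.
- **That an incomplete diary will be counted as fully observed.** The article does not say how partial diaries enter the analysis. A fuller document could settle this, and could also specify that visits per month rather than raw counts are analysed.

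It is also fair that the outcome is the last-listed secondary one, that the cost argument in the discussion is conditional, and that even the rate model has modest power at the assumed rates (at 0.25 per year it does no better than the alternatives). These points limit the weight. They do not turn the point into a mere omission: the article commits to a method for comparing outcomes, and that method suits this one poorly.

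**Conclusion.** The point holds at minor severity. The article states a method that does not fit a diary count over intervals of unequal length. Raw counts are not comparable across assessments. The ANOVA time effect is therefore distorted, and the interaction somewhat too if there is a treatment effect. The normality rule leads to a test that cannot combine repeated visits and to medians likely to be zero in both arms. The treatment comparison stays valid, but power falls from about 48% for a rate ratio to 45%, 41% or 16-24%, depending on which permitted route is taken.

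The figures rest on an assumed 1 visit per person-year, dispersion 1, a rate ratio of 0.5 and inferred intervals of 8, 13 and 13 weeks. The inequality of the intervals and the absence of observation time from the stated tests do not depend on the assumed event rate, dispersion or rate ratio. The primary outcome and the sample size are unaffected.

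**What to change.** In Statistical analysis, exempt healthcare resources use from the general rule. Analyse total visits per participant from allocation to the six-month assessment with a negative binomial model (or Poisson with robust variance), with log observation time as offset. Report the NW:CG rate ratio with its 95% CI. State the counting intervals, including the starting point of the three and six months, and show any results by period as visits per person-month instead of raw counts.

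Define observation time as time under diary follow-up, and use diary-days completed as a sensitivity analysis. If participants note a medical visit but skip routine entries, an offset of completed days would inflate the rate, possibly differently by arm. In Data collection methods, extend the request for diary data to dropouts in both arms.

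**Cost.** A few sentences, a tally of diary time from records already collected, and the same request to control dropouts. SPSS 26, the software named in the article, fits the model. There are two drawbacks: the total-period rate averages the programme and follow-up phases, which the period rates would still show, and the offset assumes that visits are recorded throughout the time counted.

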Nordic walking (NW) is one of the exercise programs that could have potential benefits for people with asthma. The main difference between NW and conventional walking is the use of two poles to boost the walk, involving for instance the upper limb during the march. It was born in Finland during the 1930s as a cross-country skiers training, and it was been developed, transitioning from skiers to university and educative fields, and then to literature and scientific publications [20, 21]. The evidence is still scarce, but it has shown benefits in exercise tolerance and HRQoL in other chronic conditions, such as metabolic syndrome, musculoskeletal disorders, Parkinson disease [22–24], cardiovascular diseases [25] and chronic obstructive pulmonary disease (COPD) [26]. In COPD, NW improved exercise tolerance (measured as meters walked in six-minute walking test-6MWT); daily physical activity levels; dyspnea; anxiety and HRQoL. COPD and asthma are both respiratory diseases that share common symptoms and signs, such as cough, dyspnea and limited air flow, as well as limited exercise tolerance. Therefore, we hypothesize that similar benefits with NW can also be achieved in patients with asthma.

Thus, the primary aim of this clinical trial is to determine whether the effect of a NW training program plus education and usual care is superior to education and usual care only, in terms of exercise tolerance and other health-related outcomes, in patients with asthma. Secondary, we aim to explore the patients’ experience with the NW program.

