### Recruitment

Subjects will be screened by physicians during consultations in the pulmonology and allergy services from the pulmonology and allergy services from A Coruña sanitary area and in primary care centres.

Subjects eligible in the study will be listed, and one researcher will be responsible to randomise blocks of six to either the NW group or control group (CG) in the same proportion. Randomization will be performed via a computer program for randomization (http://randomization.com/). The allocation will be made attending to the identification (ID) number, which will be then linked to the participants’ name in the list. The order will be unchangeable, once assigned.

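### The trial is sized on one 26 m difference in 6MWT distance, but the stated analysis covers four visits and nominates no visit, model term or contrast that tests it

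*Protocol article*

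**What the plan says.** **Sample size.** "This calculation was based on the 6MWT minimum clinically important difference in patients with asthma, which is set at 26 meters". The other inputs are "Using a standard deviation (SD) of 45.49 meters, obtained from a previous pilot study", 80% power, alpha 0.05 and 15% dropout, giving 57 per group and 114 in total. No visit is attached to the 26 m. The section does not say whether 45.49 m is the SD of a single measurement or of a change.

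**Study design.** "Assessments will take place at baseline, after 8-weeks and then at three and six months of follow-up". Data collection methods and Participant timeline confirm that the walk test is done at all four visits, T0 to T3.

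**Primary outcome.** Distance walked in the 6MWT, again with no visit named.

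**Statistical analysis.** "To compare outcomes between NW group and CG, ANOVA tests for repeated measures or Kruskal-Wallis tests will be used", the choice depending on a normality test. This sentence serves every quantitative outcome. It does not mention the group main effect, the group-by-time interaction, a contrast, a visit or how baseline enters.

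**Introduction.** The primary aim is to show that the programme is "superior to education and usual care only, in terms of exercise tolerance and other health-related outcomes".

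**The concern.** The sample size answers one question: do the groups differ by 26 m in mean distance? The stated analysis answers others. A repeated-measures ANOVA with a group factor yields two group-related terms:

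- The group main effect averages over the visits in the model. If T0 is one of them, it averages in a visit at which randomisation makes the expected difference zero.
- The group-by-time interaction asks whether the group difference varies in any way across visits. It names neither a visit nor a direction.

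The non-parametric alternative changes the question again. Kruskal-Wallis compares independent groups on one value per person, so the result of a normality test would decide whether the trial tests a longitudinal hypothesis or a cross-sectional one at an unnamed visit.

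At stake is whether the trial's main result is fixed in advance. On the same data, different readings of the sentence estimate different quantities with very different power, and one of them cannot by itself support a claim of superiority.

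**Working it through.** **1. The plan's own figure.** Two-sided alpha 0.05, power 0.80, difference 26 m, SD 45.49 m:

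n per arm = 2 × [45.49 × (1.960 + 0.842) / 26]² = 48.05

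Dropout: 48.05 / 0.85 = 56.5, so 57 per arm and 114 in total. The stated figure reproduces. Rounding up to 49 before inflating gives 58 per arm (116 in total), a trivial difference. The sizing is therefore an ordinary two-group comparison of one mean difference.

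**2. Assumptions for what follows.** 57 × 0.85 ≈ 48 completers per arm; 45.49 m is the SD at every visit (variance 2069.3); compound symmetry. The article gives no between-visit correlation ρ, so 0.5 to 0.9 is assumed. Effects at T0/T1/T2/T3 are written d_t, with mean d̄. Power is from the noncentral F distribution.

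**3. Group main effect over four visits.** It estimates d̄. Noncentrality = (48/2) × d̄² / [SD² (1 + 3ρ)/4].

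- Sustained 0/26/26/26: d̄ = 78/4 = 19.5 m. At ρ = 0.5: 24 × 380.25 / 1293.3 = 7.06, power 0.75. At ρ = 0.9: 4.77, power 0.58.
- Waning 0/26/13/0: d̄ = 39/4 = 9.75 m, power 0.26 falling to 0.19.

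**4. Group-by-time interaction, 3 df.** Noncentrality = (48/2) × Σ(d_t − d̄)² / [SD² (1 − ρ)].

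| Effect at T0/T1/T2/T3 (m) | Σ(d_t − d̄)² | Power, ρ = 0.5 | ρ = 0.7 | ρ = 0.9 |
|---|---|---|---|---|
| 0/26/26/26 | 507 | 0.83 | 0.97 | 1.00 |
| 0/26/13/0 | 464.75 | 0.79 | 0.96 | 1.00 |
| 0/26/13/13 | 338 | 0.64 | 0.87 | 1.00 |
| 0/0/0/−26 | 507 | 0.83 | 0.97 | 1.00 |

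The last row shows the lack of direction. No effect at T1 or T2 and a 26 m disadvantage for Nordic walking at T3 gives the same sum of squares, and so the same chance of significance, as a sustained 26 m benefit.

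**5. A single contrast at T1 with a true 26 m effect.**

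- Unadjusted: 24 × 676 / 2069.3 = 7.84, power 0.79.
- Baseline-adjusted (ANCOVA), 45.49 m a single-visit SD: residual variance SD²(1 − ρ²). Noncentrality is 10.45 at ρ = 0.5 and 41.3 at ρ = 0.9; power 0.89 rising to 1.00.
- Baseline-adjusted, 45.49 m the SD of change: the single-visit SD is 45.49/√[2(1 − ρ)], so the residual variance is 45.49² (1 + ρ)/2. Noncentrality is 10.45 at ρ = 0.5 and 8.25 at ρ = 0.9; power 0.89 falling to 0.81.

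**The case against.** The strongest reply is that this is a condensed article without its analysis plan, and that model terms and covariates are commonly left to that plan. Several stronger readings are tempting, and the text does not support them:

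- **That baseline is ignored.** The section is silent on baseline; it does not exclude adjustment. If T0 is a level of the repeated factor, the interaction already compares changes from baseline.
- **That the trial is underpowered.** The low figures in step 3 belong to a main-effect test that the article never selects, and its inclusion of T0 is an inference from the visit schedule. The interaction is the more natural term when T0 is in the model, and it is often well powered.
- **That a repeated-measures ANOVA cannot test 26 m.** A 1-df contrast of T1 against T0 by group, within the same model, would do so. The fault is that none is nominated.
- **That superiority could be claimed on any outcome.** The aim is loosely worded, but the Outcomes section names 6MWT distance as primary and lists the others as secondary.
- **That the type I error is about 11%.** That figure (10.9% at ρ = 0.7) assumes three separate unadjusted visit tests. The article plans no such tests.

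What survives is narrower. The article does choose a method, and that method is not the comparison it was sized for. Leaving details to an analysis plan does not reconcile the two sections, and the primary visit belongs to the definition of the primary outcome. The switch to Kruskal-Wallis is stated outright.

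**Conclusion.** The point holds in limited form, as something that should be fixed. The sample size rests on one 26 m difference and its arithmetic is sound. The stated analysis does not nominate a test of that difference, and its non-parametric branch is not a repeated-measures test.

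The consequence depends on the term chosen. For a sustained benefit, a main effect including T0 estimates 19.5 m instead of 26 m. The interaction has power of at least 0.83 in that case, but 0.64 for a 26/13/13 m profile at ρ = 0.5, and in no case shows which group did better. The main harm is thus an unfixed and possibly undirected primary claim more than a certain loss of power. The power figures rest on the assumed correlation range, compound symmetry, 48 completers per arm and, for the two omnibus terms, 45.49 m being a single-visit SD.

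**What to change.** State one primary analysis: the Nordic walking minus control difference in mean 6MWT distance at one named visit, adjusted for baseline 6MWT distance, two-sided 5%, with a 95% CI. T1, the end of the supervised programme, is the natural visit. ANCOVA or a mixed model would serve, and SPSS, already specified, fits both. Use this for the primary outcome in place of the normality-driven switch to Kruskal-Wallis. Label T2, T3 and all other outcomes as secondary, and word the primary aim to match. Say whether 45.49 m is the SD of a value or of a change.

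The change is to wording only: no new data and no more than 114 participants. The price is that one visit carries the confirmatory claim, so a benefit appearing only at T2 or T3 would be secondary evidence. The choice should be recorded before outcome data are examined.

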### Outcomes

#### Primary outcome

The primary outcome will be exercise tolerance, measured by the distance walked during the 6MWT, a reliable and validated test in patients with asthma [37], which is strongly related with important clinical outcomes as dyspnea and fatigue perceived [32].

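### A normality check on the trial data chooses between two non-equivalent tests, so the method and effect measure for the primary 6MWT comparison are not fixed in advance

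*Protocol article*

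**What the plan says.** The Statistical analysis section of the protocol article sets one rule for all quantitative outcomes. First, "Normality will be explored with Kolmogorov-Smirnov tests". Then, for the comparison of arms, "ANOVA tests for repeated measures or Kruskal-Wallis tests will be used, as appropriate in function of normality of data distribution". The same section reports normal data as mean and SD, and other data as median and quartiles.

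The rule meets this design:

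- There are two parallel arms (Study design).
- There are four visits: "Participants will be assessed at baseline (T0), post-intervention (T1), and then at three (T2) and six months (T3) follow-up" (Participant timeline).
- The primary outcome falls under the rule: "The primary outcome will be exercise tolerance, measured by the distance walked during the 6MWT". No section gives it a separate analysis.
- The trial is sized on a difference in means, the "6MWT minimum clinically important difference in patients with asthma, which is set at 26 meters" (Sample size).

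The article does not say whether normality is checked on raw values, changes or residuals, whether by arm or by visit, or which values would enter the Kruskal-Wallis test.

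**The concern.** The two branches do not answer the same question. Repeated-measures ANOVA compares mean profiles over time, and the group-by-time term carries the treatment effect. Kruskal-Wallis compares the rank distributions of independent groups. With two arms it is the Wilcoxon-Mann-Whitney test. It has no place for visit, for correlation within a person, or for a baseline covariate.

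A preliminary test on the outcome data would therefore decide the hypothesis, the effect measure and the power of the primary analysis. If the rank branch is taken, the main result need not include a between-arm difference in metres with a confidence interval, although the trial was sized on 26 m.

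A full SAP may exist and is not shown. That does not remove the point, because this is a rule that the article states. An SAP that followed it would inherit the problem.

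**Working it through.** **Inputs from the protocol (Sample size).** Difference 26 m, SD 45.49 m, power 80%, alpha 0.05, dropout 15%, N = 114 (57 per arm).

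**Assumed, not in the protocol.** Within-person correlation ρ = 0.5, 0.7 or 0.85. SD 45.49 m is taken as the SD of a single-visit value, since the text says only "Using a standard deviation (SD) of 45.49 meters, obtained from a previous pilot study". Data are normal unless stated.

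**Step 1: reproduce the stated sample size.** n per arm = 2 × [45.49 × (1.960 + 0.842) / 26]² = 48.05. Then 48.05 / 0.85 = 56.5, so 57 per arm and 114 in total. The figure reproduces with a two-sided alpha. Completers: 57 × 0.85 = 48.45, taken as 48 per arm.

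**Step 2: power at 26 m with 48 per arm.** Power = Φ(k × 26 / [s × √(2/48)] − 1.96), with √(2/48) = 0.2041. Here k = 1 for a mean comparison and k = √(3/π) = 0.977 for the rank test, its large-sample efficiency under normality.

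- Kruskal-Wallis on raw T1: s = 45.49, so Φ(0.977 × 26 / 9.286 − 1.96) = Φ(0.776) = 78% at every ρ.
- Change from baseline: s = 45.49 × √(2(1 − ρ)) = 45.49, 35.24 and 24.92.
- ANCOVA on baseline: s = 45.49 × √(1 − ρ²) = 39.40, 32.49 and 23.96.

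| Analysis | ρ = 0.5 | ρ = 0.7 | ρ = 0.85 |
|---|---|---|---|
| Kruskal-Wallis, raw T1 | 78% | 78% | 78% |
| Kruskal-Wallis, change | 78% | 94% | 99.9% |
| Group-by-time, T0 and T1 (t-test on change) | 80% | 95% | 99.9% |
| ANCOVA | 90% | 97.5% | over 99.9% |

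A simulation of 1,500 trials per setting agrees: 76-79% for raw T1; 78%, 94% and 99.7% for Kruskal-Wallis on change; 80%, 96% and 99.9% for group-by-time; 91%, 98% and 99.8% for ANCOVA.

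If 45.49 m is instead the SD of change, the single-visit SD is 45.49 / √(2(1 − ρ)) = 45.49, 58.73 and 83.05. By the same formula, power is 78%, 56% and 32% for Kruskal-Wallis on raw T1, 78% throughout on change, and 90%, 86% and 83% for ANCOVA. The order does not change.

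**Step 3: what the switch rule itself does.** In the simulation the rule takes Kruskal-Wallis on raw T1 if any of four Lilliefors-corrected checks (two arms, T0 and T1) rejects at 0.05, and otherwise takes the group-by-time test.

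- Power, normal data, rule against always group-by-time: 80% v 80% at ρ = 0.5, 92% v 96% at 0.7, 97% v 99.9% at 0.85.
- Power, skewed data (lognormal, sigma 0.5), where the rule switches in about 98-99% of trials: 92% v 78% at ρ = 0.5, 92% v 94% at 0.7, 93% v 99.7% at 0.85. ANCOVA has 88%, 97% and 99.7%.
- Type I error of the rule: about 4-7%, in line with the single tests in the same runs.

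**Step 4: how often normal data would trigger the switch.** With n = 57 per arm:

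- K-S with estimated mean and SD and no correction, any of eight arm-by-visit cells: about 0%.
- Lilliefors-corrected, T1 only, two arms: about 8-10%.
- Lilliefors-corrected, any of eight cells: about 28% (26-29% across runs).

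With 48 per arm and four cells it was 15-20%.

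**The case against.** Several stronger conclusions are tempting, and the protocol does not support them.

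- *The rank test cannot use the baseline.* It has no covariate term, but it can be run on change scores, and the text does not exclude that. Its power is then close to ANCOVA at high correlation (94% v 97% at 0.7). The large gap, 78% v 97%, belongs only to raw T1 values.
- *The switch inflates the error rate.* The simulation shows no such effect. Separate tests at three follow-up visits would give about 11%, but that is multiplicity over visits and not a result of the normality rule. A figure of about 27% would need a patient's four values to be pooled as independent, which no section proposes.
- *One trial in four would switch by chance.* That needs a Lilliefors correction, eight checks, and a switch on any rejection. Under other readings the rate is near zero.
- *Results could not be set against 26 m at all.* Medians and quartiles would still be reported in metres. What is missing is a between-arm estimate with an interval.

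It is also fair to say that normality is only to be explored, and that a rank test can be the better one: with skewed data and correlation 0.5 it has 92% power against 78% for the group-by-time test. For ordinal scales and sparse counts a rank test is reasonable.

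What remains is that the sentence on comparing the arms makes the test depend on normality, that this covers the primary outcome, and that the two tests are not counterparts. A possible gain under skewness supports a named rank-based sensitivity analysis. It does not support choosing the primary method from the data.

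**Conclusion.** The point holds in this form and should be fixed: as written, the method and effect measure for the primary 6MWT comparison depend on a pre-test of the trial data, and the fallback is not the counterpart of the main analysis. The text alone supports this, without any assumption.

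The size is conditional. It rests on an assumed within-person correlation, on reading 45.49 m as a single-visit SD, on normal data and on 48 completers per arm. Against baseline-adjusted ANCOVA the rank branch loses about 12 points of power at correlation 0.5. At 0.7 it loses about 3 points on change scores and about 20 on raw T1 values. At 0.85 the loss is negligible on change scores and over 20 points on raw values. With strong skewness and low correlation the order can reverse. The harm shown is an unfixed question and a possible loss of power. Bias or a raised false-positive rate from the switch is not shown. The stated sample size is not in dispute.

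**What to change.** Remove the normality-driven choice for 6MWT distance. Name one analysis that is used whatever the Kolmogorov-Smirnov result: ANCOVA, or a linear mixed model with baseline, group, visit and group-by-visit. Report the post-intervention (T1) between-arm difference in metres with a 95% confidence interval. Check the residuals, and list a rank-based or bootstrap analysis of the same contrast as a named sensitivity analysis.

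Possible wording: *6MWT distance will be analysed with a linear mixed model including baseline distance, group, visit and group-by-visit. The primary estimate is the adjusted difference between arms at T1, in metres, with a 95% confidence interval. Residuals will be examined. A rank-based analysis of the T1 contrast will be reported as a sensitivity analysis and will not replace the primary one.*

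The cost is wording only, recorded as a protocol modification in the way the Ethics section already provides. It uses data already planned, and N stays at 114. The one downside is some loss of power if the data are strongly skewed and the correlation is low (88% for ANCOVA against 92% for Kruskal-Wallis on raw T1 in the skewed setting at 0.5).
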